9.5 Inducement

Subjects shall be reimbursed for their transport to attend all visits to the health centre. In addition, five $US per day of hospitalization will be provided to cover the hospital fees and the transportation of the family visiting the patient.


Appendix 1. Definition of severe falciparum malaria[[4]](#footnote-5)

**Severe manifestation of *P. falciparum* malaria in adults**

**Clinical manifestations**

- prostration,
- impaired consciousness,
- respiratory distress (metabolic acidosis),
- multiple convulsions,
- circulatory collapse,
- pulmonary oedema (radiological),
- abnormal bleeding,
- jaundice,
- haemoglobinurea.

**Laboratory findings**

- severe anaemia (haemoglobin < 5 g/dl, haematocrit < 15%),
- hypoglycaemia (blood glucose < 2.2 mmol/l or 40 mg/dl),
- acidosis (plasma bicarbonate < 15 mmol/l),
- hyperlactataemia (venous lactic acid > 5 mmol/l),
- hyperparasitaemia (> 4% in non-immune patients),
- renal impairment (serum creatinine above normal range for age).

Appendix 2. Medications (with antimalarial activity) that should not be used during the study period

- chloroquine, amodiaquine;
- quinine, quinidine;
- mefloquine, halofantrine, lumefantrine;
- artemisinin and its derivatives (artemether, arteether, artesunate, dihydroartemisinin);
- proguanil, chlorproguanil, pyrimethamine;
- sulfadoxine, sulfalene, sulfamethoxazole, dapsone;
- primaquine;
- atovaquone;
- antibiotics: tetracycline*, doxycycline, erythromycin, azythromycin, clindamycin, rifampicin, trimethoprim;
- pentamidine.

* Tetracycline eye ointments can be used.

Appendix 3. Dosing chart of ARtesunAte

Tablets containing 50 mg of artesunate. Doses will be rounded to the nearest quarter-tablet. The dose in mg and in # tablets will be recorded in the CRF Dose Administration Form. These are the same doses as used in the ‘Clinical investigation of in-vivo susceptibility of *P. falciparum* to artesunate in Western Cambodia’

| **Weight (kg)** | **Artesunate** | |
| --- | --- | --- |
| **4 mg/kg (OD)** | |
| Mg | **Tablets** (50mg) |
| **30-32** | 125 | **2 1/2** |
| **33-34** | 137.5 | **2 3/4** |
| **35** | 137.5 | **2 3/4** |
| **36-39** | 150 | **3** |
| **40** | 162.5 | **3 1/4** |
| **41-42** | 162.5 | **3 1/4** |
| **43-45** | 175 | **3 1/2** |
| **46** | 187.5 | **3 3/4** |
| **47-48** | 187.5 | **3 3/4** |
| **49-51** | 200 | **4** |
| **52-53** | 212.5 | **4 1/4** |
| **54** | 212.5 | **4 1/4** |
| **55-57** | 225 | **4 1/2** |
| **58-59** | 237.5 | **4 3/4** |
| **60** | 237.5 | **4 3/4** |
| **61-64** | 250 | **5** |
| **65** | 262.5 | **5 1/4** |
| **66-67** | 262.5 | **5 1/4** |
| **68-70** | 275 | **5 1/2** |

Appendix 4. Classification of treatment outcomes[[5]](#footnote-6)

**Early treatment failure**

- danger signs or severe malaria on day 1, 2 or 3 in the presence of parasitaemia;
- parasitaemia on day 2 higher than on day 0, irrespective of axillary temperature;
- parasitaemia on day 3 with axillary temperature ≥ 37.5 ºC;
- parasitaemia on day 3 ≥ 25% of count on day 0.

**Late treatment failure**

**Late clinical failure**

- danger signs or severe malaria in the presence of parasitaemia on any day between day 4 and day 28 (day 42) in patients who did not previously meet any of the criteria of early treatment failure;
- presence of parasitaemia on any day between day 4 and day 28 with axillary temperature
  ≥ 37.5 ºC (or history of fever) in patients who did not previously meet any of the criteria of early treatment failure

**Late parasitological failure**

- presence of parasitaemia on any day between day 7 and day 28 with axillary temperature
  < 37.5 ºC in patients who did not previously meet any of the criteria of early treatment failure or late clinical failure

**Adequate clinical and parasitological response**

- absence of parasitaemia on day 28, irrespective of axillary temperature, in patients who did not previously meet any of the criteria of early treatment failure, late clinical failure or late parasitological failure

Appendix 5. Case screening form

**.**

**.**

| **Case screening form** | | | | | |
| --- | --- | --- | --- | --- | --- |
| Health centre name: | | | | | Study number: |
| Locality: | | | | | Patient screening number: |
| District: | | | | | Date of visit (dd-mmm-yyyy): |
| Province: | | | | |  |
| **Demographic data** | | | | | |
| Date of birth (dd-mmm-yyyy): | | | or estimated age:       in:  months or  years | | |
| Height (cm): | Weight (kg): | |  | | |
| Sex:  Male  Female | | |
| If female, is the patient pregnant?  Yes  No  Not sure | | | | | |
| If pregnant, provide the date of the last menstrual period (dd-mmm-yyyy): | | | | | |
| **Pre-treatment temperature** | | | | | |
| History of fever in previous 24 h?  Yes  No | | | | | |
| Temperature:       ºC  Axillary  Tympanic  Rectal  Oral | | | | | |
| **Thick and thin blood smears for estimation of *P. falciparum*****parasite counts** | | | | | |
| Species:  *P. falciparum*  *P. vivax*  *P. ovale*  *P. malariae* | | | | | |
| Were species other than *P. falciparum* present?  Yes  No **(If yes, patient is not eligible).** | | | | | |
| Approximate number of *P. falciparum* asexual parasites:  Presence of 10–100 parasites / 6 white blood cells?  Yes  No **(If no, patient is not eligible)** | | | | | |
| Presence of *P. falciparum* gametocytes?  Yes  No | | | | | |
| Has a blood sample for PCR been collected?  Yes  No | | | | | |
| Haemoglobin:       g/dl | | Haematocrit:       % | | | |
| **Urinary analysis (pregnancy test for female patients)** | | | | | |
| Result of pregnancy test:  Positive  Negative **(If positive, patient is not eligible)** | | | | | |
| **Inclusion criteria** | | | | | |
| - age > 18years - mono-infection with *P. falciparum* confirmed by positive blood smear (i.e. no mixed infection) - parasitaemia between 10000 and 100000/µl of asexual forms - measured temperature (depending on method of measurement) or history of fever within previous 24 h - ability to swallow oral medication - ability and willingness to comply with the study protocol for the duration of the study and to comply with the study visit schedule - absence of severe malnutrition (defined as per protocol) | | | | | |
| Does the patient meet all the inclusion criteria?  Yes  No **(If no, patient is not eligible)** | | | | | |
| **Case screening form (page 2)** | | | | | |
| **Exclusion criteria** | | | | | |
| - signs and symptoms of severe or complicated malaria requiring parenteral treatment according to WHO criteria (Appendix 1) - mixed or mono-infection with another *Plasmodium* species detected by microscopy - severe malnutrition - febrile conditions caused by diseases other than malaria or other known underlying chronic or severe diseases - regular medication which interferes with antimalarial pharmacokinetics - history of hypersensitivity reactions or contraindications to the medicine tested - positive pregnancy test or breastfeeding - unable to or unwilling to take contraceptives. | | | | | |
| Does the patient meet any of the exclusion criteria?  Yes  No **(If yes, the patient is not eligible)** | | | | | |
| If yes, please specify the reason for exclusion: | | | | | |
| **Patient informed consent and assent** | | | | | |
| Consent form signed:  Yes  No | | | | Patient identity number:  Date (dd-mmm-yyyy): | |
| Assent form signed:  Yes  No | | | |

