3.6 Exclusion criteria

- presence of signs of severe falciparum malaria according to the definitions of WHO (Appendix 1);
- mixed or mono-infection with another Plasmodium species detected by microscopy;
- presence of severe malnutrition (defined as a child whose growth standard is below –3 z-score, has symmetrical oedema involving at least the feet or has a mid-upper arm circumference < 110 mm);
- presence of febrile conditions due to diseases other than malaria (e.g. acute lower respiratory tract infection, severe diarrhoea with dehydration) or other known underlying chronic or severe diseases (e.g. cardiac, renal and hepatic diseases, HIV/AIDS);
- regular medication, which may interfere with antimalarial pharmacokinetics;
- history of hypersensitivity reactions or contraindications to any of the medicine(s) being tested or used as alternative treatment(s); and
- a positive pregnancy test or breastfeeding (include this criterion only if adults are included);
- unable to or unwilling to take a pregnancy test or contraceptives (for women of child-bearing age);
- previous antimalarial drug intake in the past 48 hours;
- patients presenting with spenectomy.

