Appendix 7. Case report forms

| **Case report form: follow-up day 0** | | | | | | | | | | |
| --- | --- | --- | --- | --- | --- | --- | --- | --- | --- | --- |
| Health centre name: | | | | | | | | Study number: | | |
| Locality: | | | | | | | | Patient identity number: | | |
| District: | | | | | | | | Date of visit (dd-mmm-yyyy): | | |
| Province: | | | | | | | |  | | |
| **Demographic data** | | | | | | | | | | |
| Date of birth (dd-mmm-yyyy): | | | | | or estimated age:       in:  months or  years | | | | | |
| Height (cm): | | Weight (kg): | | | Sex:  Male  Female | | | | | |
| If female, is the patient pregnant?  Yes  No  Not sure **(If yes, patient is not eligible).** | | | | | | | | | | |
| If pregnant, provide the date of the last menstrual period (dd-mmm-yyyy): | | | | | | | | | | |
| **Pre-treatment temperature** | | | | | | | | | | |
| History of fever in previous 24 h?  Yes  No | | | | | | | | | | |
| Temperature:       ºC  Axillary  Tympanic  Rectal  Oral | | | | | | | | | | |
| **Thick blood smears for** ***P. falciparum*: quantitative parasite counts and qualitative gametocyte counts** | | | | | | | | | | |
| Average number of asexual *P. falciparum* parasites/l at Day 0 H0: | | | | | | | Average number of asexual *P. falciparum* parasites/l at Day 0 H12: | | | |
| Presence of *P. falciparum* gametocytes at Day 0 H0?  Yes  No | | | | | | | Presence of *P. falciparum* gametocytes at Day 0 H0?  Yes  No | | | |
| Were species other than *P. falciparum* present?  Yes  No **(If yes, patient is not eligible).** | | | | | | | | | | |
| If yes, which species?  *P. vivax*  *P. ovale*  *P. malariae* | | | | | | | | | | |
| Has blood sample for PCR been collected?  Yes  No | | | | | | | | | | |
| **Urinary test for antimalarial drugs** | | | | | | | | | | |
| Test used: | | | | Test result:  Positive  Negative | | | | | | |
| **Prior medication** | | | | | | | | | | |
| All prior medication, including natural remedies and homeopathic medicines, taken within the previous 14 days should be reported in this section. | | | | | | | | | | |
| Has the patient taken any prior antimalarial medication?  Yes  No. If yes, please specify below. Either the date of stopping or the ‘ongoing’ box should be checked. | | | | | | | | | | |
| Medicine name (generic name) | Dates | | Ongoing  (Yes = ) | | | Total daily dose and unit (e.g. 400 mg) | | | Route of administration | Indication for use |
|  | Start: | |  | | |  | | |  |  |
| Stop: | |

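### The Appendix 5 screening form's exclusion list differs materially from section 3.6 on four of ten criteria, so a patient whom the protocol excludes can be passed on the form

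*Protocol*

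**What the plan says.** Section 3.6 of the protocol lists 10 exclusion criteria. Among them are "previous antimalarial drug intake in the past 48 hours", "patients presenting with spenectomy" (splenectomy is evidently meant), "regular medication, which may interfere with antimalarial pharmacokinetics" and "history of hypersensitivity reactions or contraindications to any of the medicine(s) being tested or used as alternative treatment(s". Another excludes women of child-bearing age who cannot or will not take a pregnancy test or contraceptives.

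The Appendix 5 case screening form does not refer back to section 3.6 for its exclusions. It prints 8 items of its own and then asks "Does the patient meet any of the exclusion criteria", with an instruction that a yes makes the patient ineligible. Its drug-reaction item is "history of hypersensitivity reactions or contraindications to the medicine tested" and its medication item is "regular medication which interferes with antimalarial pharmacokinetics".

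The day 0 case report form in Appendix 7 asks "Has the patient taken any prior antimalarial medication" and collects medication from the previous 14 days with start and stop dates.

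**The concern.** The decision line on the form sits directly under the form's own list, so the natural reading is that it refers to that list. Staff who answer it that way can truthfully enter *No* for a patient whom section 3.6 excludes.

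There are two consequences, both small. The first is patient safety. Rescue treatment is part of the design, and section 4.3 names mefloquine after repeated vomiting and quinine with doxycycline for severe malaria. The form has no item for a known reaction to these drugs. A woman who refuses the pregnancy test is not caught by the form's exclusion list either, although section 5.2.8 calls artesunate contraindicated in the first trimester.

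The second is consistency of the study population. A patient who took another antimalarial shortly before enrolment may still have that drug in the blood. That bears on parasite clearance time, the clearance slope and day-3 positivity, which section 5 lists as end-points.

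**Working it through.** The protocol gives no figure to reproduce, so the check is an item-by-item comparison of the two lists.

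| Section 3.6 criterion | Appendix 5 form | Difference |
| --- | --- | --- |
| 1. Signs of severe malaria | Present, with an added qualifier that it requires parenteral treatment; same reference to Appendix 1 | Wording only |
| 2. Mixed or other species | Present | None |
| 3. Severe malnutrition | Present; definition left to the protocol | None in substance |
| 4. Other febrile, chronic or severe disease | Present without the examples | None in substance |
| 5. Interfering regular medication | Present; the conditional *may* is lost | Wording only |
| 6. Hypersensitivity or contraindication, test or alternative medicines | Test medicine only | Materially narrower |
| 7. Positive pregnancy test or breastfeeding | Present | None |
| 8. Unable or unwilling: pregnancy test or contraceptives | Contraceptives only | Materially narrower |
| 9. Antimalarial intake in past 48 hours | Not on the list | Absent |
| 10. Splenectomy | Not on the list | Absent |

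Counts:

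- Absent: 2 (items 9 and 10).
- Materially narrower: 2 (items 6 and 8).
- Material differences: 2 + 2 = 4 of 10.
- Wording only: 2 (items 1 and 5). Every literal difference in scope: 4 + 2 = 6 of 10.
- Carried over: 4 (items 2, 3, 4 and 7). Check: 4 + 2 + 2 = 8, the number of items on the form, and 8 + 2 = 10.

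Next, is each material gap closed elsewhere?

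- **48-hour intake.** The day 0 form records it, so it can be found. However, section 6.2 assigns the case report form to enrolled patients, and the prior-antimalarial line has no ineligibility instruction, whereas the pregnancy and species lines on the same form do.
- **Rescue-drug reaction.** No other screening item asks about reactions to other medicines. A complete medical history (section 5.2.1) could reveal one, but the form would not treat it as excluding.
- **Pregnancy-test refusal.** This is partly covered by the form's test-result line with its stop, by the willingness-to-comply inclusion item, and by the consent statement in section 9.2. The result line offers only positive or negative, so a refusal has no box.
- **Splenectomy.** Only the medical history could reveal it.

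Section 3.8 is not an explicit later catch. Its enrolment-violation entries name severe malaria on day 0 and unmet inclusion criteria, and do not name a breached exclusion criterion.

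**The case against.** The strongest reply is that section 3.6 is complete and governs. Sections 6.1 and 6.2 require all enrolment criteria to be met, and section 6.1 describes the form as a record of information and observations. The decision line does not expressly limit itself to the printed list. On this view the mismatch is clerical, and it matters only if staff decide from the form alone. Most of this stands and is why the point is minor. It does not remove the point, because a form that prints its own list and attaches a stop to it is the working eligibility tool, and the two texts disagree.

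Three stronger readings might be inferred, and the document supports none of them.

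- **That the missing rescue-drug wording exposes lumefantrine-reactive patients to harm they would otherwise avoid.** Section 4.3 gives artemether-lumefantrine for treatment failure, but section 9.4 gives the same drug to anyone who cannot be enrolled. Exclusion would not by itself spare such a patient. The safety argument therefore rests on mefloquine, quinine and doxycycline, which are used only after repeated vomiting or for severe malaria.
- **That half of the list fails to carry over.** A count of five needs one of the two wording-only differences to be included and the other left out. A consistent standard gives four (material) or six (literal).
- **That the eligibility rule has changed or the end-points are biased.** The rule in section 3.6 is intact, and nothing in the document shows that any such patient would be enrolled, or how many.

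**Conclusion.** The point holds as a minor inconsistency between the eligibility criteria and the form that applies them. Four of the 10 section 3.6 criteria differ materially on the form and two more differ in wording. This counts items and does not measure risk. The number of patients affected, and any shift in the clearance or day-3 results, cannot be derived from the document.

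The conclusion assumes that at least some screening decisions are taken from the form's own list. If staff always check section 3.6 as well, the mismatch has no effect. Which of the four gaps matters most is a judgement: the 48-hour item bears most on the clearance end-points, while the rescue-drug and pregnancy-test items bear on safety. Correction is worthwhile because it is specific and costs almost nothing.

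**What to change.** Reconcile the exclusion list in Appendix 5 to section 3.6:

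- add antimalarial intake in the past 48 hours, and splenectomy;
- extend the hypersensitivity and contraindication item to medicines used as alternative treatment;
- extend the refusal item to the pregnancy test as well as contraceptives;
- restore *may* in the interfering-medication item;
- remove the parenteral-treatment qualifier from the severe-malaria item;
- add a box to the pregnancy-test line: not done/refused (woman of child-bearing age: not eligible).

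Do not paste section 3.6 verbatim. It contains a drafting note about when to include the pregnancy criterion, a malnutrition definition framed for children in a study of patients over 18, and a misspelling of splenectomy.

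The cost is a reprint of a two-page form and possibly a few more screening exclusions.

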Appendix 6. Schedule of follow-up activities

|  | Day | | | | | | | | | |
| --- | --- | --- | --- | --- | --- | --- | --- | --- | --- | --- |
| 0 | 1 | 2 | 3 | 7 | 14 | 21 | 28 | Any other |  |
| **Procedure** |  |  |  |  |  |  |  |  |  |  |
| Clinical assessment | X | X | X | X | X | X | X | X | (X) |  |
| Temperature | X | X | X | X | X | X | X | X | (X) |  |
| Blood slide for parasite count | X |  | X | X | X | X | X | X | (X) |  |
| Urine sample | (X) |  |  |  |  |  |  |  |  |  |
| Blood for:  genotyping  molecular markers  antimalarial blood concentration | X  X  11 X | X |  |  | X | X | X | X | X |  |
| Treatment |  |  |  |  |  |  |  |  |  |  |
| Medicine to be tested from day 0 to day 6 included | X | X | X | X |  |  |  |  |  |  |
| Rescue treatment |  | (X) | (X) | (X) | (X) | (X) | (X) | (X) | (X) |  |

Parentheses denote conditional or optional activities. For example, treatment would be given on days 1 and 2 only for 3-day dosing. On day 1, the patient should be examined for parasitaemia if he or she has any danger signs. Rescue treatment could be given on any day, provided that the patient meets the criteria for treatment failure. Extra days are any days other than regularly scheduled follow-up days when the patient returns to the facility because of recurrence of symptoms. On extra days, blood slides may be taken routinely or at the request of the clinical staff.

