The critical question is whether artemisinin derivatives are actually failing or not against current recommended total dosage (12 mg/kg) or higher dosage. Since artemisinin resistance is not just limited to the Thai-Cambodia border, but may have extended to or emerged on the Thai-Myanmar, China-Myanmar and Cambodia-Viet Nam borders, confirmatory artemisinin resistance through monotherapy in vivo studies and molecular fingerprinting of parasite genomes to track artemisinin resistance (gene flow) moving around the region is even more important now.

The trial described here proposes to assess the PCT and the efficacy after 4mg/kg oral artesunate over 7 days. The results of this study will be compared to recent data from patients in Cambodia and Thailand treated with equivalent doses of artemisinin derivatives.

2. Objectives

The primary objective of this study is to assess the PCT and efficacy of artesunate 4mg/kg/day in the treatment of uncomplicated *P. falciparum* malaria in Kawthaung (Tanintharyi Division) in Myanmar.

The specific objectives are:

- to measure the PCT with blood sampling for parasite counts twelve hourly and to measure clinical and parasitological efficacy of artesunate 4mg/kg/day over 7 days in patients aged > 18 years, suffering from uncomplicated falciparum malaria
- to determine the proportion with early treatment failures, late clinical failures, late parasitological failures or adequate clinical and parasitological response as indicators of efficacy
- to differentiate recrudescence from new infection by polymerase chain reaction (PCR) analysis
- to evaluate the number of adverse events
- to formulate recommendations and to enable the Ministry of Health to make informed decisions about whether the current national antimalarial treatment guidelines should be updated. The results of this study will indicate if artemisinin resistance is present in Myanmar which allows a better mapping of the situation of artemisinin resistance in the region and indicate if containment effort should be started.

The secondary objectives are:

- to determine the polymorphism of molecular markers for antimalarial resistance; and
- to determine the blood concentration of artesunate and dihydroartemisinin

3. Methods

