### 5.2.4 Microscopic blood examination

Thick and thin blood films for parasite counts will be obtained and examined at screening on day 0 to confirm adherence to the inclusion and exclusion criteria. Thick or thin blood films will be also examined every 12 hours until PCT and on days 1, 2, 3, 4, until negativation, 7 (if after PCT), 14, 21, 28 or on any other day if the patient returns spontaneously and parasitological reassessment is required. Specimens will be labelled anonymously (screening number or study number, day of follow-up, date).

A fresh Giemsa stain dilution will be prepared at least once a day and possibly more often, depending on the number of slides to be processed. Giemsa-stained thick and thin blood films will be examined at a magnification of 1000 to identify the parasite species and to determine the parasite density.

Three blood slides per patient will be obtained: two thick blood smears and one thin blood smear. One slide will then be stained rapidly (10% Giemsa for 10–15 min) for initial screening, while the others will be retained. If the patient is subsequently enrolled, the second slide will be stained more carefully (e.g. 2.5–3% Giemsa for 45–60 min), and slower staining will also be used for all slides obtained at follow-up visits. The study number of the patient, the date and the day of follow-up will be recorded either on the frosted edge of the slide or on the glass with a permanent glass pen.

The thick blood smear for initial screening will be used to count the numbers of asexual parasites and white blood cells in a limited number of microscopic fields. The adequate parasitaemia for enrolment is at least one parasite for every six white blood cells, corresponding to approximately 1000 asexual parasites per microlitre.

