6.2 Follow-up

Patients who meet all the enrolment criteria will be given a personal identification number and will receive treatment only after the study has been fully explained to them and they have willingly provided informed consent. Any person who decides not to participate in the study will be examined, treated and followed-up by the health facility staff according to the standard of care established by the Ministry of Health.

The basic follow-up schedule is summarized in Appendix 6. A case report form (Appendix 7) and a serious adverse event report form (Appendix 8) will be used to record the general information and clinical observations on each patient enrolled into the study. The appointment schedule will be clearly explained, and a follow-up card with a personal identification number will be provided.

The day a patient is enrolled and receives the first dose of medicine is designated ‘day 0’. All antimalarial treatment will be given by a study team member under supervision. Enrolled patients will be observed for at least 30 min after treatment to ensure that they do not vomit the medicine. If vomiting occurs within 30 min of treatment, the full treatment dose will be repeated. Ancillary treatment, such as antipyretics, will be provided if necessary to patients by the study team and documented on the case report form. Patients with persistent vomiting (i.e. necessitating more than a single repeat dose) will be excluded from the study and immediately referred to the health facility staff for appropriate management.

Thereafter, patients are required to undergo regular clinical reassessment. Blood films for parasite counts will be made twice a day (12 hourly) til parasite clearance and then on day 7 and then weekly for the remainder of the follow-up period, i.e. on days 14, 21, and 28. Patients will be advised to return on any day during the follow-up period if symptoms return and not to wait for the next scheduled visit day. Clinical reassessment will be sufficiently thorough to ensure patient safety and will include assessment not only for potential treatment failure but also for potential adverse reactions to the medicine. Additionally, blood films will be obtained whenever parasitological reassessment is requested by the clinical staff.

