**Day 1**

- clinical assessment; referral in cases of severe malaria or danger signs;
- measurement of axillary temperature;
- parasitological assessment in cases of severe malaria or danger signs;
- treatment, second dose or alternative treatment in case of early treatment failure.

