|  | Start: | |  | | |  | | |  |  |
| Stop: | |
|  | Start: | |  | | |  | | |  |  |
| Stop: | |

| **Case report form: follow-up day 0 (page 2)** | | | | | |
| --- | --- | --- | --- | --- | --- |
| **Medication administration** | | | | | |
| Name(s) of antimalarial drug(s) | | Time of dose (hh:min) | Number of tablets | Did the patient vomit? | Time of vomiting (hh:min) |
|  | |  |  | Yes  No |  |
|  | |  |  | Yes  No |  |
| Name(s) of other medicine(s) |  | | | | |
|  | |  |  | Yes  No |  |
|  | |  |  | Yes  No |  |

| **Case report form: follow-up day 1** | | | | | |
| --- | --- | --- | --- | --- | --- |
| Study number: | | | | | |
| Patient identity number: | | | | | |
| Date of visit (dd-mmm-yyyy): | | | | | |
| **Clinical status** | | | | | |
| Presence of danger signs or signs of severe or complicated malaria?  Yes  No  If yes, perform thick blood smear. | | | | | |
| Temperature:       ºC  Axillary  Tympanic  Rectal  Oral | | | | | |
| **Thick blood smears for estimation of *P. falciparum* parasite counts** | | | | | |
| Average number of asexual *P. falciparum* parasites/l at Day 1 H0: | | | Average number of asexual *P. falciparum* parasites/l at Day 1 H12: | | |
| Presence of *P. falciparum* gametocytes at Day 1 H0?  Yes  No | | | Presence of *P. falciparum* gametocytes at Day 1 H12?  Yes  No | | |
| Were species other than *P. falciparum* present?  Yes  No | | | | | |
| If yes, which species?  *P. vivax*  *P. ovale*  *P. malariae* | | | | | |
| **Adverse events** | | | | | |
| Presence of an adverse event?  Yes  No | | | | | |
| If yes, name the adverse event: | | | | | |
| Is it a serious adverse event?  Yes  No. If yes, inform the sponsor. | | | | | |
| **Medication administration** | | | | | |
| Name(s) of antimalarial drug(s) | Time of dose (hh:min) | Number of tablets | | Did the patient vomit? | Time of vomiting (hh:min) |
|  |  |  | | Yes  No |  |
|  |  |  | | Yes  No |  |
| Name(s) of other medicine(s) |  | | | | |
|  |  |  | | Yes  No |  |
|  |  |  | | Yes  No |  |

| **Case report form: follow-up day 2** | | | | | |
| --- | --- | --- | --- | --- | --- |
| Study number: | | | | | |
| Patient identity number: | | | | | |
| Date of visit (dd-mmm-yyyy): | | | | | |
| **Clinical status** | | | | | |
| Presence of danger signs or signs of severe or complicated malaria?  Yes  No | | | | | |
| Temperature:       ºC  Axillary  Tympanic  Rectal  Oral | | | | | |

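### Appendix 6 makes the day-1 blood film conditional on danger signs and shows no 12-hourly films, contradicting the 12-hourly counts on which PCT and the clearance slope rest; the day-1 CRF contradicts itself.

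*Protocol*

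**What the plan says.** **Text requiring 12-hourly films.** The first specific objective in section 2 is "to measure the PCT with blood sampling for parasite counts twelve hourly". Section 5.2.4 states "Thick or thin blood films will be also examined every 12 hours until PCT and on days 1, 2, 3, 4, until negativation", which names day 1 and attaches no condition to it. Section 6.2 states "Blood films for parasite counts will be made twice a day (12 hourly) til parasite clearance".

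**Text that differs.** In the Appendix 6 table the row "Blood slide for parasite count" is marked on days 0, 2, 3, 7, 14, 21 and 28. Day 1 is blank, and no cell indicates two films a day. The note beneath reads "On day 1, the patient should be examined for parasitaemia if he or she has any danger signs". The day-1 activity list in the same appendix gives "parasitological assessment in cases of severe malaria or danger signs".

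**The case report form.** In Appendix 7, the danger-sign question on the day-1 form is followed by "If yes, perform thick blood smear". The same form then has fields for the parasite count at H0 and H12 of day 1, with no condition. The forms for days 0, 2 and 3 also have H0 and H12 count fields.

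**End-points that use the films.** Section 5 lists PCT, the slope of the log-linear clearance curve, the reduction rate at 48 hours and positivity at day 3. Section 8.2 repeats them as analyses.

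**The concern.** PCT is part of the primary objective, and the results are to be compared with data from Cambodia and Thailand. Under the clearance the protocol expects, most of the fall in parasitaemia is over within two days, so the 24 h and 36 h films carry much of the information on slope and on the time of clearance. Those are the films that Appendix 6 makes conditional.

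The appendix cannot be dismissed as decoration. Section 6.2 names it as the summary of the basic follow-up schedule and also says the protocol's schedule must be followed for data integrity. A site that worked from the table could comply with one part of the protocol and still miss the counts another part needs. Missed early counts cannot be recovered.

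There is a smaller inconsistency about day 3. Section 6.2 says "Blood films for parasite counts will be made twice a day (12 hourly) til parasite clearance and then on day 7", which taken alone gives no day-3 film to a patient who has already cleared, whereas Appendix 6 has one for everyone.

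**Working it through.** There is no stated figure to reproduce, because the point is a conflict of text. The calculation shows what each schedule would deliver.

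**Inputs from the protocol**
- Parasitaemia at entry 10,000 to 100,000/µl (section 3.5).
- Expected reduction about 10,000-fold per cycle, clearance usually under 48 h (section 5.1.1).
- A film is negative when 1000 white cells show no parasites, with 6000 white cells/µl assumed (section 5.2.4). Detection limit = 6000 / 1000 = 6/µl.

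**Assumptions**
- A 48 h cycle and log-linear decline with no lag.
- Day 1 H0 = 24 h, day 1 H12 = 36 h, day 2 H0 = 48 h, day 3 H0 = 72 h.
- The PCT bracket runs from the last positive film to the first negative film.

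**Formula.** Count at t hours = P0 × R^(−t/48), where R is the reduction per 48 h. A film is positive if the count is at least 6/µl. Time to the limit = 48 × log10(P0/6) / log10(R).

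**Check against the protocol's expectation.** With R = 10,000 the count falls tenfold every 12 h. Time to the limit is 12 × log10(10,000/6) = 38.7 h at the lowest entry count and 12 × log10(100,000/6) = 50.7 h at the highest. This is broadly in line with clearance usually under 48 h.

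**Example, P0 = 30,000, R = 10,000.** Counts at 0, 12, 24, 36 and 48 h are 30,000, 3,000, 300, 30 and 3/µl. Four are positive on the 12-hourly schedule. The literal Appendix 6 row (0, 48, 72 h, day 7) sees only the first. If every 12-hourly film except 24 h and 36 h is taken, two are seen.

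Each cell below gives the number of positive films, then the PCT bracket in hours.

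| R per 48 h | P0 (/µl) | 12-hourly | Day-1 films missed | Appendix 6 row, literal |
|---|---|---|---|---|
| 10,000 | 10,000 | 4; 36–48 | 2; 12–48 | 1; 0–48 |
| 10,000 | 30,000 | 4; 36–48 | 2; 12–48 | 1; 0–48 |
| 10,000 | 100,000 | 5; 48–60 | 3; 48–60 | 2; 48–72 |
| 1,000 | 30,000 | 5; 48–60 | 3; 48–60 | 2; 48–72 |
| 100 | 30,000 | 8; 84–96 | 6; 84–96 | 3; 72–168 |

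One positive count gives no slope. Two give a line with nothing left over to check it. In slower clearers, missing day 1 removes two slope points but leaves the 12 h bracket intact; the literal row widens the bracket to 24 h or, at R = 100, to 96 h.

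**Day 3.** The Appendix 6 table has a day-3 slide, its list for days 2 and 3 asks for parasitology without condition, and the day-3 form has H0 and H12 fields. Only section 6.2 taken alone skips it. A patient still positive at 72 h has a film under any of these texts, so what section 6.2 would leave unobserved is the negative status of patients who had already cleared.

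**The case against.** The 12-hourly design is fixed in three places in the body, and the form prompts for H0 and H12 counts on days 0 to 3. The note to Appendix 6 still mentions 3-day dosing, which suggests generic text left in place. On this view staff would take the films and the appendix is an editing slip. That makes the worst case less likely, but it does not settle the matter: nothing says that the body or the form overrides Appendix 6.

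The objection also rules out three stronger readings.

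- *The day-1 form allows a film only with danger signs.* A reader might infer this from the conditional line. The form does not say only, and its unconditional H0 and H12 fields point the other way. It contradicts itself.
- *Day-3 positivity, the basis of the sample size in section 8.1, would mostly be assumed rather than observed.* That requires following section 6.2 alone and setting aside Appendix 6 and the form. Even then the likely effect is small, since patients who cleared by 48 or 60 h would mostly be negative at 72 h.
- *Only slow clearers would have a slope.* At 100,000/µl and the expected clearance, the 48 h count is about 10/µl, above the 6/µl limit, so two points remain even under the literal table. With the day-0 H12 film on the form, a patient at 30,000/µl also has two.

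The 48 h reduction rate keeps its day-0 and day-2 films throughout.

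**Conclusion.** The contradiction holds. Appendix 6, in its table, note and day-1 list, conflicts with the Objectives and with sections 5.2.4 and 6.2, and the day-1 form is inconsistent within itself. The texts must be reconciled because two named end-points depend on the answer.

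The loss is conditional on the site following Appendix 6. Taken literally, that schedule would remove most of the information on PCT and slope in normally clearing patients who enter at 10,000 or 30,000/µl: from four counts and a 12 h bracket to one count and a 48 h bracket, or to two counts and a 36 h bracket if only day 1 is missed. At 100,000/µl the loss is smaller. These sizes rest on the assumed 48 h cycle and no lag. That staff would work from the appendix is an inference, not something the protocol states.

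The day-3 inconsistency is secondary and probably changes few classifications.

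**What to change.** 1. In the Appendix 6 blood-slide row, enter films every 12 hours until clearance, filling the day-1 cell, in agreement with sections 2, 5.2.4 and 6.2.
2. Delete the danger-sign condition on the day-1 film from the note to the table and from the day-1 list, and delete the conditional smear line on the day-1 form. The H0 and H12 fields stay as they are. Section 6.2 already allows extra films whenever clinical staff ask for them.
3. In sections 5.2.4 and 6.2, state that the day-3 (72 h) film is taken and read in every patient, including those already negative, so that they agree with Appendix 6 and the form.

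The cost is a set of text edits. The body already requires the 12-hourly films, and patients are in hospital for the first 7 days (section 3.3), so the added work is at most one slide for each patient who clears early.
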